### Eligibility criteria and screening procedures

The ASD group is male children aged 4–10 years diagnosed with ASD according to the Diagnostic and Statistical Manual of Mental Disorders, Fifth Edition (DSM-5) criteria, based on the evaluations performed by the child development team [35]. ASD diagnosis is confirmed by a developmental paediatrician through evaluations of medical history and clinical symptoms. The inclusion criteria for the ASD group are as stated: (1) male children aged 4–10 years who meet the DSM-5 criteria for ASD; and (2) whose parents or legal authorized representative (LAR) is willing to provide informed consent on their behalf. The exclusion criteria for the ASD group are as stated: (1) children below age of 4 years and above 10 years old; or (2) children who do not meet the case definition; or (3) children who have are on medications such as Ritalin and antipsychotics, anti-inflammatory, antioxidant drugs, or antibiotics in the three months prior to sample collection.

The TD group included healthy male children aged 4–10 years, with no history of early developmental delay, learning difficulties, or any other neurological or psychiatric conditions. Participants must not have been on medications such as Ritalin, antipsychotics, anti-inflammatory, antioxidant drugs or antibiotics in the three months prior to sample collection. Children with first degree relatives diagnosed with neurological, psychiatric, or neurodevelopmental disorders are excluded. TD children are defined as those achieving age-appropriate developmental milestones across gross motor, fine motor, language, cognitive, social-emotional and behavioural development. In Malaysia, routine health examinations monitor infant and child growth and developmental progress. Children were classified as TD if parents reported no developmental concerns from healthcare providers and no learning difficulties noted by schoolteachers.

### Recruitment

Children with ASD are identified by the developmental paediatrician at HTJ, Seremban, whereas TD healthy children are recruited from daycare centres or TABIKA KEMAS in Seremban. Data collection is performed by a trained graduate research assistant, acting as the research enumerator commenced on 24^th^ August 2024. Parents or legal guardians are given the study information sheet and to obtain their signed consent forms by the research enumerator. Participant recruitment and data collection are estimated to be completed in June 2026. Fig 2 below illustrated the study protocol workflow.

**Fig 2 pone.0338801.g002:**
[figure not shown]
Flow diagram of study protocol workflow.

### Saliva and stool sample collection and analysis

Prior to saliva sample collection, participants will refrain from eating or drinking for at least 30 minutes, if this condition is not met, participants will be asked to gently rinse mouth with clean water before sampling. Saliva samples will be collected using 1 ml Copan eNAT^®^ swabs and 1 ml Copan SMART-eNAT^®^ (Cat. No. 70U001N, Copan Italia S.p.A., Brescia, Italy), both of which are guanidine-thiocyanate-based medium that inactivate microorganisms and stabilizes microbial DNA [36,37]. Two saliva samples will be collected on the day of recruitment and transferred to the laboratory at room temperature. Upon arrival, all the samples will be vortexed in the collection tubes until sample is homogenous, and divided into two aliquots as follows: 0.5 ml will be placed into four cryovials, respectively. All samples will be parafilm sealed, labelled with the collection date and specific study ID number (excluding personal information), and subsequently stored in a −80 °C freezer.

Stool samples will be collected using the 9 ml DNA/RNA Shield™ Faecal Collection Tube (Cat. No. R1101, Zymo Research, Irvine, CA, USA) [38] and 1 ml Copan SMART-eNAT^®^ (Cat. No. 70U001N, Copan Italia S.p.A., Brescia, Italy) [37]. Parents/LAR will receive a reminder via text message and a tutorial video outlining the timing and methods for self-collection of two faecal samples at home, along with instructions for storing the samples at room temperature. Once self-collection is completed, parents/LAR are required to notify the researchers to arrange transportation of the samples to the Institute for Research, Development, and Innovation (IRDI) research laboratory at IMU University, Kuala Lumpur, located approximately 50 km away. Faecal samples will be vortexed in the collection tubes until sample is homogenous, and the resulting stool slurry will be divided into two aliquots as follows: 0.5 ml will be placed into four cryovials, respectively. All samples will be immediately parafilm sealed, labelled with the collection date and specific study ID number (excluding personal information), and stored in a −80 °C freezer. All samples will be transported on dry ice to AGTC Genomics, Kuala Lumpur for further analysis.

DNA will be extracted using Zymo Quick-DNA MagBead Plus Kit. The purity of the extracted DNA samples will be assessed using Implen NanoQuant Spectrophotometer, and DNA libraries will be prepared using the DNA library Prep (Illumina, CA, USA) according to the manufacturer’s instructions. The prepared DNA libraries will be sequenced on Illumina Novaseq 6000 system (Illumina, CA, USA) at PE150. Libraries will be normalised to 1.75nM and pooled before loading into the NovaSeq sequencing platform. Demultiplexing of samples will be performed using Illumina DRAGEN BioIT Platform (Illumina) v3.9. CCMetagen pipeline will be used for taxonomic identification. Raw sequence reads (FASTQ files) will be trimmed and analysed using One Codex (https://www.onecodex.com/) to assess alpha diversity (as measured by the Shannon index) and to identify relative microbial abundances within the oral and gut microbiome of each participant.

The quality of raw reads will be examined with MultiQC [39]. Adapter sequences and low-quality reads (length < 50 bp or phred < 30) will be removed. To avoid potential human genome contamination, reads will be mapped against the hg38 human genome reference database (UCSC Genome Browser) using the Burrows–Wheeler Aligner (BWA) [40]. Unmapped reads (without human genome) will be used for downstream analyses. Bacterial taxonomic composition will be characterised using Kraken2 (v2.0.7, https://github.com/DerrickWood/kraken2) with the NCBI RefSeq database [41]. Kraken2, an ultrafast taxon-assigning tool, performs ultrafast taxonomic classification by aligning k-mers from the sequence data and assigning taxa based on the lowest common ancestor (LCA). Taxonomic abundances will then be re-estimated using Bracken (Bayesian Re-estimation of Abundance with KrakEN, v2.6), a Bayesian algorithm for recalculating species-level abundance [42]. HUMAnN3.5 (the HMP unified metabolic analysis network, https://github.com/biobakery/humann/tree/2.9) will be used to identify the functional genes/pathways associated with microbiome gene markers [43]. HUMAnN3.5 integrates with MetaPhlAn4 (Metagenomic Phylogenetic Analysis, v4, https://github.com/biobakery/MetaPhlAn4) for taxonomic profiling, utilizing its ChocoPhlAn pangenome database alongside the MetCyc, MinPath and UniRef90 databases [44]. From the HUMAnN2 output, gene family abundances with ≥90% match to UniRef90 will be used to convert this information to KEGG Orthologs (KOs: functional genes). Subsequently, the relative abundance of functional genes will be calculated based on the absolute abundance of all KOs for each sample.

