### Study Population and setting

Male children between 4–10 years old who comply with the protocol definition and inclusion criteria will be enrolled as participants. Cases are defined as male children diagnosed with ASD and receiving under follow-up care at the Paediatric Clinic at HTJ. Controls are defined as age-matched, TD healthy male children from daycare centres near IMU Healthcare and TABIKA KEMAS in Seremban. These locations were selected based on convenience sampling. Cases and controls are matched within using an age range of ±6 months.

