### Statistical analysis plan

Data analysis will be conducted using R software and its available packages. The differences in microbiota profiles, socio-demographic factors, emotional and eating behaviour, and nutritional status between children with ASD and TD children will be compared using the chi-square/Fisher’s exact test and ANOVA where appropriate. Student’s t-test will be applied to compare BMI and age between groups. Pre-filtering and inference of correlations will be performed using the Sparse Correlations for Compositional Data (SparCC) correlation metric [66], with a minimum R-value threshold of 0.35. SparCC will be used to correlate salivary and faecal bacterial markers detected in saliva and faecal samples from the same child. The associations between microbiota profiles, socio-demographic factors, emotional and eating behaviour, autism severity, sleep quality, gastrointestinal symptoms, and nutritional status among children with ASD will be modelled using mixed-effects logistic regression (MELR) model and random forest. Normality, linearity, homoscedasticity, and multi-collinearity will be assessed to ensure that the assumptions of regression models are met. Potential confounders, including age, and socioeconomic status will be adjusted for fixed effects. Model assumptions will be performed using DHARMa package in R to assess dispersion, zero-inflation and overall fit [67]. In case of heteroscedasticity or overdispersion, corrective strategies will include the use of an observation-level random effect, modelling dispersion or zero-inflation with glmmTMB [68], or applying bias-reduced logistic regression (Firth correction) [69] or bootstrap inference to mitigate small-sample bias [70]. Study results are expected in December 2026.

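### The saliva rule lets a boy who has recently eaten or drunk rinse and be sampled, so oral profiles may mix two pre-sampling conditions in proportions that could differ between cases and controls

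*Protocol article*

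**What the plan says.** In the section Saliva and stool sample collection and analysis, the standard condition is that "participants will refrain from eating or drinking for at least 30 minutes". The fallback follows at once: "if this condition is not met, participants will be asked to gently rinse mouth with clean water before sampling". For a child who misses the 30 minutes, the text offers no wait, deferral or second appointment. On timing, it says: "Two saliva samples will be collected on the day of recruitment and transferred to the laboratory at room temperature".

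The section Study Population and setting fixes where each group comes from. Cases are boys "receiving under follow-up care at the Paediatric Clinic at HTJ"; controls are "TD healthy male children from daycare centres near IMU Healthcare and TABIKA KEMAS in Seremban". On matching it says: "Cases and controls are matched within using an age range of ±6 months". All participants are male.

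The section Statistical analysis plan says: "Potential confounders, including age, and socioeconomic status will be adjusted for fixed effects". The condition under which saliva was taken is not among the factors named.

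**The concern.** By setting a 30-minute rule, the protocol itself treats recent intake as relevant to the saliva sample. The fallback does not restore that interval, and the rinse is not applied to every child. Either rule applied uniformly would give more comparable samples than a mixture of the two.

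A mixture matters for the group comparison only if its proportions differ by group. Here group is tied to recruitment setting, and time since the last meal or drink can plausibly vary with setting. If it does, any effect of recent intake plus rinsing would enter the ASD-TD comparison of oral profiles and could be taken for a difference due to ASD. Oral microbiota is part of the primary aim, and the Sample size section names microbial beta diversity as a primary outcome.

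**Working it through.** The documents state no figure on this point, so there is none to reproduce. The check has two parts.

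**1. Reading the sections together**

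- Two conditions are allowed by the stated rule: no intake for at least 30 minutes, or a shorter interval followed by a water rinse.
- Saliva is taken on the day of recruitment. Cases are recruited through the hospital clinic, and controls through daycare centres or TABIKA KEMAS (Recruitment; Study Population and setting).
- Matching is on age only, in an all-male sample, so it does not balance the sampling condition.
- The confounders named are age and socioeconomic status. The wording is open-ended, but the sampling condition is not mentioned.

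The mix could therefore differ by group, and nothing stated in the article would correct for it.

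**2. Illustration of size (assumed values)**

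Inputs from the Sample size section: 40 per group as recruited, or 30 per group if 60 participants remain.

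Assumptions, none of them from the documents:

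- the eaten-and-rinsed condition shifts a continuous oral measure, such as the Shannon index, by 0.3 to 0.8 SD;
- the rinsed share differs between groups by 20 to 40 percentage points;
- there is no true group difference, and the test is two-sided at 5%.

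Formulas:

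- spurious difference b = (difference in rinsed share) × (shift in SD);
- standard error se = √(2/n), with n per group and within-group SD 1, ignoring the small extra variance from the mixture;
- rejection probability = Φ(b/se − 1.96) + Φ(−b/se − 1.96).

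Worked case, n = 40: b = 0.40 × 0.5 = 0.20 SD; se = √(2/40) = 0.224; b/se = 0.894. The rejection probability is Φ(−1.066) + Φ(−2.854) = 0.143 + 0.002 = 0.145.

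| Difference in rinsed share | Shift (SD) | b (SD) | n = 30 per group | n = 40 per group |
|---|---|---|---|---|
| 0 | any | 0 | 5.0% | 5.0% |
| 20 points | 0.3 | 0.06 | 5.6% | 5.8% |
| 20 points | 0.5 | 0.10 | 6.7% | 7.3% |
| 40 points | 0.5 | 0.20 | 12.1% | 14.5% |
| 40 points | 0.8 | 0.32 | 23.6% | 29.9% |

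Using the noncentral t instead of the normal changes little: 11.9% and 14.3% at 0.20 SD, and 23.0% and 29.3% at 0.32 SD, for n = 30 and n = 40.

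The table uses a single continuous measure. It does not give the error rate of a beta-diversity test, for which the documents provide no distances or variances.

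**The case against.** The strongest reply is that the protocol contains no contradiction here. It sets one rule with one fallback and words both identically for cases and controls. For boys aged 4 to 10, half of them with ASD, a fallback is practical. The list of confounders is not exhaustive, and a collection form or fuller plan that cannot be seen may record time since intake. The harm also needs the rinsed share to differ by group, yet the article gives no meal times, clinic hours or frequency of the fallback, and does not expressly say where controls give saliva. Both inputs to the illustration are assumed.

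Most of this stands, and it limits the point. It does not remove it, because the two-condition rule is stated in the text and does not depend on a missing record.

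A reader might infer several stronger things that the documents do not support:

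- **That the oral comparison is biased.** Two conditions arise only if some boys miss the 30 minutes, and bias arises only if the shares differ by group. Neither is documented.
- **That boys with ASD rinse less well, or that rinsing changes the oral profile in a known way.** The article says nothing on either.
- **That the saliva-stool correlations would show a false ASD difference.** As described, SparCC relates markers in saliva and stool from the same child; it is not an ASD-TD contrast. Rinsing could only make those correlations noisier or distort them.
- **That the sampling condition goes unrecorded.** The article does not mention recording, but a condensed article cannot settle this.

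**Conclusion.** The point holds in a limited form. The stated rule allows saliva from two pre-sampling conditions, group is tied to recruitment setting, and nothing in the article balances or adjusts for the condition. The ASD-TD oral comparison could therefore be biased. Stool analyses are not affected.

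The size and direction of any bias are unknown. Under the assumed ranges the spurious difference is 0.06 to 0.32 SD, and the false-positive rate of a nominal 5% test is about 6% to 30%. It stays at 5% if the rinsed shares are equal. These figures show what could happen and are not estimates for this study. The matter is minor, and worth acting on because the remedy is cheap.

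**What to change.** For the remaining recruitment, make waiting until 30 minutes have passed the first option, for example by taking saliva after height and weight, and keep the rinse for a child who cannot wait. The wait should not be planned around the questionnaires: the Reimbursement section ties the voucher to receipt of the stool sample and the parents' questionnaire, so the questionnaire may be returned later.

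Record minutes since last intake and rinse status for every child, and report both by group. Repeat the oral ASD-TD analyses excluding rinsed samples, or adjusting for rinse status. For samples already taken, do this where rinse status was recorded or can be recovered; where it cannot, say so as a limitation.

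The cost is a short wait that some children may not tolerate, one extra data entry and one sensitivity analysis. Inability to wait could itself differ by group, which is why rinse status must still be recorded. Changing the procedure during collection also creates an earlier and a later regime; the collection date on each sample label allows these to be told apart.

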### Data collection sheet

This sheet contains two sections as follows: (1) Information on participant and family demographics (child’s gender, age, gestational age, birth weight, parent’s age, ethnicity, occupation, education level, and household income); and (2) ASD medical history (age of first presentation, first presenting complaint, family history of ASD or other neurodevelopmental disorders (NDDs)) and other relevant medical conditions, if applicable.

### Anthropometric data

Stadiometer (SECA 213 Portable, Germany) and weighing scale (TANITA HD-319, Japan) will be used to obtain children’s height to the nearest 0.1 cm and weight to the nearest 0.1 kg. The BMI-for-age z score (BAZ), height-for-age z score (HAZ), and weight-for-age z score (WAZ) will be calculated using the WHO AnthroPlus Software version 1.0.4 [45]. BAZ, HAZ and WAZ classifications will be determined based on the WHO Child Growth Standards for children under five years of age and the WHO Growth Reference for children aged five years and above [46–48].

### Nutritional status and dietary assessment

A Subjective Global Nutrition Assessment (SGNA) will be utilised to determine the nutritional status of the children [49]. SGNA evaluates nutritional status in two main categories: Nutrition Focused Medical History (NFMH) and Physical Exam (PE). NFMH includes evaluating the appropriateness of current height and weight for age, changes in body weight, dietary adequacy, gastrointestinal symptoms, functional capacity, and metabolic aspects of disease. PE evaluates subcutaneous fat loss, muscle wasting, and nutrition-related oedema. The combined NFMH and PE evaluation will generate an overall SGNA ranking of normal/well-nourished, moderately malnourished, severely malnourished [49].

Dietary intake of the children will be obtained through parental interviews, using 3-day dietary recalls (two weekdays and one weekend day). To assist with the food intake portion size estimation, pictures of household measuring tools will be provided. Detailed information about the food and beverages consumed, such as cooking methods and brand names (if applicable), will be recorded. Nutrient analysis will be generated using the Nutritionist Pro^TM^ Diet Analysis software (Axxya Systems LLC, USA) and the Malaysian Food Composition Database (MyFCD). Nutrient adequacy will be assessed by comparing the intake to the Malaysian Recommended Nutrient Intakes (RNIs) [50]. Adequate intake will be defined as meeting or exceeding 100% of the RNI for macro- and micronutrients Portion size estimation in dietary assessment has been validated as reliable [51]. As dietary data will be parent-reported, research assistant will verify accuracy by reconfirming food intake during data entry prior to nutrient analysis. Basal metabolic rate (BMR) will also be calculated to identify potential underreporting or overreporting of energy intake.

Anthropometric measurements will be conducted by trained research assistant ([name]), a registered dietitian who completed standardized anthropometric assessment training measurement according to the standardized guideline by ISAK [52]. Observer and assessor training will be provided to research staff while obtaining data on 3-days dietary recall, with peer review and error checks to ensure data reliability.

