## Abstract

**Background:**

Autism Spectrum Disorder (ASD) is a neurodevelopmental disorder characterised by persistent deficits in social communication and the presence of restricted, repetitive behaviours or interests. Previous literature has identified a link between the gut and ASD; however, the underlying mechanisms remain unclear. Gut microbiota dysbiosis has been extensively reported in cohort studies of ASD, and specific microbial metabolites or by-products may serve as potential biomarkers for ASD. Additionally, children with ASD often exhibit food refusal, have a limited food repertoire and display a tendency to consume the same foods frequently; thus, these behaviours increase their risk of malnutrition (over-nutrition or under-nutrition) compared to typically developing (TD) healthy children. This study primarily aims to identify oral and gut microbiota among children with ASD and TD healthy children. The secondary aim is to determine the associations between oral and gut microbiota with nutritional status among children with ASD. The findings will enhance understanding of the aetiology of ASD and inform early intervention strategies to mitigate disease severity and early identification of malnutrition in genetically at-risk children.

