**Methods and analysis:**

This observational, age-matched, case-control study is conducted in Malaysia among 40 male children with ASD and age-matched with 40 TD healthy controls aged 4–10 years. The dependent variables include the microbiota profile, identified through metagenomic sequencing analysis of saliva and faecal samples, and autism severity, assessed through validated questionnaires. Independent variables include nutritional status, determined through Subjective Global Nutrition Assessment (SGNA), anthropometry and dietary measurements, gastrointestinal symptoms, eating behaviour, behavioural profile, and sleep quality. Data collection is expected to be completed by June 2026. The study nature may limit causality establishment. Analyses will use chi-square/ANOVA for group comparisons, SparCC for microbiota correlations, and mixed-effects logistic regression to model associations.

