Children with ASD are frequently associated with disruptive mealtime behaviours, such as severe food refusal, a limited food repertoire, and high-frequency single-food intake [8]. These behaviours are closely related to sensory processing difficulties, such as aversion to specific textures, smells, and tastes [9]. Consequently, children with ASD are at an elevated risk of poor nutritional status. A local study conducted among 224 children with ASD in Kuala Lumpur reported that the prevalence of underweight, stunting, wasting/thinness and overweight/obesity were 9.3%, 8.0%, 4.0%, and 21.5%, respectively [10]. Another recent study in central region of Malaysia (Selangor, Kuala Lumpur, and Negeri Sembilan) involving a total sample size of 150 children with ASD documented that 15% of the children were underweight, and 52% were overweight and obese [11]. Although most children had adequate total energy and protein intakes, their fat intake exceeded the recommended levels [10]. Moreover, the majority of the children did not meet the Recommended Nutrient Intake (RNI) requirements for several key nutrients, including fibre (99.6%), thiamine (67.4%), vitamin C (50.9%), vitamin D (98.2%), vitamin E (74.6%), vitamin B12 (64.3%), folate (88.8%), calcium (90.2%), and zinc (77.2%) [10]. Therefore, a comprehensive understanding of the nutritional risks faced by children with ASD is essential for healthcare professionals to develop effective, targeted nutritional interventions.

Research has shown that children with ASD may exhibit altered nutrient metabolism, including deficiencies in essentials vitamins and minerals, which could contribute to the development and progression of the disorder. For example, studies have reported lower levels of vitamins B6 and B12 in children with ASD, both of are critical for neurological function [12–14]. Dietary habits are considered one of the main factors influencing the diversity of human gut microbiota [15]. Furthermore, host genetics, dietary habits, gut physiology, hygiene level, stress, and physical activity influence the gut microbiota. The human gut “metagenome” is a complex consortium of trillions of microbes, whose collective genomes contain over 100 times as many genes as the human eukaryote genome [16]. This essential “organ,” the microbiome, provides the host with protection against pathogens, enhancement of immune system and metabolic capabilities, as well as modulation of gastrointestinal (GI) development [17].

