### Sample size

This study aims to compare the microbial community structure between the ASD and TD healthy groups and within the groups, generating plausible distances relevant to the study objectives. Beta diversity is used to estimate the sample size or statistical power for this study. The recommended sample size is 60 participants, determined based on calculations using data from a study conducted by Li et al. [31]. Due to the limited availability of similar studies, this prior research served as a reference to obtain appropriate variance estimates [31]. The total study sample size of 60 participants has been adjusted to account for a possible 30% dropout rate; thus, this study aims to recruit 80 participants (40 children with ASD and 40 TD healthy children). The primary outcomes are microbial beta diversity and nutritional status. Secondary microbiota comparisons will be adjusted for multiple testing using the Benjamini-Hochberg false discovery rate, and post-hoc power analyses will be conducted to assess adequacy for multivariate models.

The study included only male children to eliminate potential gender bias, as the male predominance in ASD has been well-documented in epidemiological studies and widely recognised in the field [32–34]. This approach also ensures greater homogeneity in the demographic and microbiome datasets, thereby enhancing the precision and reliability of the findings.

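### Nutritional status is a primary outcome, but the tool assigned to it (SGNA) has no over-nutrition level, and the protocol does not say whether SGNA or BMI-for-age defines the outcome

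*Protocol article*

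**What the plan says.** The Sample size section of the protocol article states: "The primary outcomes are microbial beta diversity and nutritional status". It does not name the variable that stands for nutritional status.

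Two places define it, and they differ:

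- Nutritional status and dietary assessment: "A Subjective Global Nutrition Assessment (SGNA) will be utilised to determine the nutritional status of the children". On the output: "The combined NFMH and PE evaluation will generate an overall SGNA ranking of normal/well-nourished, moderately malnourished, severely malnourished". On the examination part, "PE evaluates subcutaneous fat loss, muscle wasting, and nutrition-related oedema". The history part includes a judgement on height and weight for age, but the article does not say how excess weight is scored.
- Abstract, Methods and analysis: "nutritional status, determined through Subjective Global Nutrition Assessment (SGNA), anthropometry and dietary measurements".

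The Anthropometric data section adds z-scores for BMI, height and weight for age (BAZ, HAZ, WAZ), with WHO classifications. The Statistical analysis plan section lists nutritional status among the variables compared between groups and modelled. Separately, it applies a t-test to BMI.

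On the construct itself, the abstract says of the eating behaviours of children with ASD that "these behaviours increase their risk of malnutrition (over-nutrition or under-nutrition) compared to typically developing (TD) healthy children". The Background section cites two Malaysian studies of children with ASD. One, with 224 children, found 9.3% underweight and 21.5% overweight or obese. In the other, with 150 children, "15% of the children were underweight, and 52% were overweight and obese".

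**The concern.** The study counts malnutrition in both directions, and its own background figures put excess weight above underweight. The scale named for the outcome runs in one direction, from well nourished to severely malnourished, and the signs listed for its physical examination are loss of fat, loss of muscle and oedema. A boy with obesity and no wasting has no rank of his own on it.

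The same boy can therefore fall into different classes on SGNA and on BMI-for-age, and the protocol does not say which one counts. Two things are at stake. If SGNA is taken as the outcome, an ASD–TD difference in over-nutrition would not show in that analysis as such, and microbiota models using the SGNA rank could not separate boys with excess weight from the rest. If the choice is left open, it can be made among disagreeing measures after the data have been seen, which naming a primary outcome is meant to prevent.

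**Working it through.** The plan gives no sample size, power or significance figure for nutritional status, so there is no stated figure to reproduce. The check compares the definitions and then sizes the group that SGNA cannot identify.

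**1. Can each measure record over-nutrition?**

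| Measure | Where | Over-nutrition level |
|---|---|---|
| SGNA overall rank | Nutritional status and dietary assessment | None among the three ranks |
| BMI-for-age z-score and WHO class | Anthropometric data | Yes |
| BMI, t-test | Statistical analysis plan | Only as a higher mean |
| Nutritional status (primary) | Sample size | Measure not named |

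**2. Expected numbers.** Inputs: 40 boys with ASD (Sample size) and the two local studies (Background). Expected count = group size × prevalence.

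- Overweight or obese: 40 × 0.215 = 8.6; 40 × 0.52 = 20.8.
- Underweight: 40 × 0.093 = 3.7; 40 × 0.15 = 6.0.
- With 30 per group (the 60 participants before the dropout allowance): overweight 30 × 0.215 = 6.5 to 30 × 0.52 = 15.6; underweight 30 × 0.093 = 2.8 to 30 × 0.15 = 4.5.

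**3. Share of weight problems that are excess weight.** Overweight ÷ (overweight + underweight):

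- 224-child study: 21.5 / (21.5 + 9.3) = 70%.
- 150-child study: 52 / (52 + 15) = 78%.

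On a broader count the first study is about even. Adding its stunting (8.0%) and thinness (4.0%) to underweight, as if no child had two of these, gives 9.3 + 8.0 + 4.0 = 21.3%, against 21.5% overweight or obese.

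**4. Power, as illustration only.** The documents give no prevalence for TD boys, so every control rate below is an assumption. The method is exact enumeration of two binomials with the uncorrected chi-square test, two-sided 5%, 40 per group.

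| Contrast | ASD rate (cited) | TD rate (assumed) | Power |
|---|---|---|---|
| Overweight/obese | 52% | 21.5% / 25% / 30% | 0.82 / 0.71 / 0.53 |
| Overweight/obese | 21.5% | 10% / 15% / 25% / 30% | 0.30 / 0.12 / 0.07 / 0.14 |
| Underweight | 15% | 9.3% / 8% / 5% | 0.13 / 0.18 / 0.35 |

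Only with the higher ASD figure does a BMI-for-age class have a clear advantage. With the lower one, power for overweight is 7% to 30%, no better than for underweight. The underweight row is also not the power of SGNA, which scores much more than weight.

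**The case against.** The strongest reply is that over-nutrition is not lost from the study. The abstract lists anthropometry and diet beside SGNA, BMI-for-age is classified by WHO criteria, BMI is compared between groups, and the literature review singles out BMI within nutritional status. A reader might infer that a true ASD–TD difference in over-nutrition would disappear. The documents do not support that: it would be absent only from analyses in which SGNA is the nutritional-status variable, and no section says SGNA alone is the primary outcome.

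A reader might also infer that every overweight boy will be ranked normal/well-nourished. That is not established. The history part considers weight for age, dietary adequacy and gastrointestinal symptoms, the scoring of excess weight is not given, and such a boy could be ranked malnourished on other items. This does not rescue the scale, though: if excess weight did count as malnutrition, obese and wasted boys could share a rank, and SGNA still could not tell them apart.

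Nor does the analysis section name the SGNA normal rank as a reference class, so a claim that the planned models are biased towards zero describes a model the plan does not specify.

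Finally, a condensed article may leave the exact primary variable to a fuller document. That would answer a complaint about missing detail. It does not answer this one, because the article itself assigns nutritional status to SGNA in one place and to three measures in another.

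**Conclusion.** The point holds in limited form. Nutritional status is a primary outcome with two differing definitions, and the tool assigned to it in the dedicated section has no level for a condition that the abstract counts as malnutrition. About 9 to 21 of 40 boys with ASD would be in that position, against about 4 to 6 underweight, if the study sample resembles the two cited local studies. That excess weight is the commoner problem holds on the weight measure; on the broadest count of under-nutrition, the smaller of the two overweight figures is about matched.

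The harm is confined to analyses that use the SGNA rank as the nutritional-status variable. No power loss can be fixed from the documents, because TD rates are not given and the answer depends heavily on which cited ASD rate is used. Since height, weight and BAZ are collected in any case, no data are lost. This should be fixed, but it does not threaten the study as a whole.

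**What to change.** Reconcile the abstract and the Sample size, Anthropometric data, and Nutritional status and dietary assessment sections so that one variable defines the primary nutritional-status outcome. The natural choice is the BMI-for-age class (under / healthy / over) from the WHO classification already planned, with the continuous BAZ analysed alongside. Report SGNA as a separate secondary measure of under-nutrition, and do not use its normal/well-nourished rank as the healthy reference group in any comparison or model.

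The cost is protocol and analysis-plan wording; no new measurement is needed. Data collection is due to end in June 2026 and results are expected in December 2026, so the change should be recorded before analysis. The downside is that SGNA is no longer the lead measure. Another explicit rule for combining the measures would also settle the definition, provided it keeps over-nutrition and under-nutrition distinguishable.
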